# Evaluation of the effectiveness of infrared light-emitting diode photobiomodulation in children with sleep bruxism

**DOI:** 10.1097/MD.0000000000017193

**Published:** 2019-09-20

**Keywords:** children, electromyography, LED, salivary biomarkers, sleep bruxism

## Abstract

**Background::**

Sleep bruxism is a masticatory muscle activity characterized as rhythmic (phasic) or nonrhythmic (tonic). In children and adolescents, etiological factors, such as breathing pattern and sleep quality, have recently been addressed in studies investigating sleep bruxism. New therapies for adults, such as botulinum toxin, have been investigated, but such techniques are not applicable for individuals in the growth and development phase.

**Methods::**

The participants will be 76 children, which will be randomly allocated to a control group, that is group 1, absence of bruxism; group 2, children with bruxism treated with infrared light-emitting diode (LED); and group 3, bruxism treated with occlusal splint. All participants will be submitted to a clinical evaluation to evaluate muscle activity and salivary biomarkers, before and after treatments. Muscle activity will be verified by electromyography of muscles mastication, masseter and temporal, and salivary biomarkers observed will be cortisol and dopamine levels.

**Discussion::**

Photobiomodulation therapy has piqued the interest of researchers, as this noninvasive method has demonstrated positive results in problems related to muscle tissues. This document describes the protocol for a proposed study to evaluate morphological and psychosocial aspects in children and adolescents with awake bruxism and their responses to photobiomodulation therapy with infrared LED.

**Clinical trials::**

https://clinicaltrials.gov/ct2/show/NCT03710174

## Introduction

1

Sleep bruxism is a masticatory muscle activity during sleep that is characterized as rhythmic (phasic) or nonrhythmic (tonic) and is not a movement disorder or a sleep disorder in otherwise healthy individuals1. Clenching and/or grinding the teeth while sleeping is denominated primary or sleep bruxism, whereas clenching/grinding the teeth during the day is denominated secondary or awake bruxism.^[1]^ The etiology of bruxism is widely discussed in the literature. Studies investigating emotional disorders have increasingly found an association with parafunctional muscle activity, such as bruxism. According to Wieckiewicz et al (2014),^[2]^ bruxism may be related to the occlusion or may be caused entirely by psychological stimuli. Indeed, individuals with a more aggressive, compulsive, or controlling profile are reported to be more susceptible to the development of bruxism.^[3]^

Stress can be measured using salivary biomarkers, such as cortisol, which is a hormone activated by the hypothalamus-pituitary-adrenal axis in response to a physical or psychological stressor. Repeated exposure to stress can trigger excessive cortisol secretion, which can have harmful effects on one's health.^[4]^ Dopamine is a neurotransmitter from the family of catecholamines and phenylethylamines that, among other functions, contributes to the control of movements, learning, mood, emotions, cognition, and memory.^[5]^ Like cortisol, dopamine can also be quantified based on salivary levels.^[6]^ Changes in dopamine levels have been related to neuropsychiatric disorders, such as Parkinson disease, in which diminished concentrations of dopamine are found in the nigrastriatal pathway, or schizophrenia, both of which are diseases that affect the motricity of muscles.^[6]^ Although some studies have evaluated the dopamine concentration in salivary fluid,^[5,6]^ no studies have investigated dopamine concentrations in patients with bruxism, despite the fact that this problem affects the motricity of oral muscles.

The surrounding environment exerts a direct influence on the reflexes of the body in response to a stressor. All impressions related to the external environment are processed and evaluated by the central nervous system, more precisely the limbic system and hypothalamus, which provoke adequate emotions and stimulate the sympathetic nervous system, releasing adrenaline, which triggers changes, such as increases in the respiratory rate, heart rate, muscle tension, glucose level, and blood pressure. Any information that provokes such a response is recognized as a stressor.^[7,8]^ The effects of the suppression of emotions and motor activities overload the function of the organism, resulting in various neuromuscular disorders.^[9]^

Clenching the teeth has been associated with anxious tendencies.^[10]^ Anxiety in children is a common occurrence in pediatric clinical practice. The prevalence of anxiety ranges from 2.5% to 5% in the general population and 10.6% to 24% in children with bruxism.^[11]^ Differently from adults, symptoms related to anxiety change with the different phases of development in children, which often makes identification difficult. Therefore, if not detected at an early age, bruxism could lead to consequences that compromise the function of the stomatognathic system, exerting a negative effect on quality of life.

The most indicated treatment for bruxism is an occlusal adjustment with the use of a bite plate (Michigan splint).^[12]^ Alternative treatments for muscle disorders have been developed and have demonstrated good results, such as low-level laser therapy (LLLT). LLLT has been administered to acupuncture points in adults with temporomandibular disorder,^[13]^ with a significant difference found in signs and symptoms of the disorder following application of the technique. The authors attribute the success of therapy to the reduction in pain and muscle relaxation promoted by LLLT. Physiologically, LLLT is a form of biostimulation involving the occurrence of increased blood circulation, vasodilatation, analgesia, an anti-inflammatory effect, a reduction in edema, and the acceleration of the healing process of injured tissues. Photobiomodulation therapy with a light-emitting diode (LED) has also been used for the treatment of muscle disorders. Silva et al. (2015)^[14]^ established a treatment protocol for fibromyalgia including the use of LED. Besides the physiological gains that occur with LLLT, the authors consider LED treatment accessible because of its low cost and more durable equipment, making this a viable treatment option.

## Aim

2

The aim of this project is to establish a protocol for evaluation of effectiveness of photobiomodulation therapy in children with sleep bruxism.

## Material and methods

3

This project was evaluated by the human research ethics committee of University Nove de Julho (certificate of approval: 1.333.636) and clinical trials ID NCT03710174. The sample size was calculated considering α = 0.05 and an 80% power (n = 16 per group), to which 20% will be added to compensate for possible dropouts (n = 19 per group), totaling 76 children and adolescents. Additionally, sample size was calculated for internal validity by using the results of a previous study that evaluated the decrease in signs and symptoms of TMD after occlusal splint therapy (Restrepo et al^[15]^). Considering a mean difference between treatments equal to 2 (SD = 2), 3 groups, power of test of 80%, and an alpha level of 0.05, a minimum of 30 subjects should be included in each group.

The protocol is in accordance with the 2013 SPIRIT (Standard Protocol Items: Recommendations for Interventional Trials) Statement. The SPIRIT checklist can be found as an additional file and Figure 1 is the SPIRIT figure. SPIRIT was developed to provide guidance in the form of a checklist of recommended items to include in a clinical trial protocol, to help improve its content and quality (Fig. 2).

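### The sample size paragraph gives 19 and 30 per group at the same alpha and power, the 30 does not follow from its inputs, and the total of 76 fits four groups although three are listed

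*Protocol article*

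**What the plan says.** The sample size paragraph (Protocol article, Material and methods) contains two calculations.

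- First: "The sample size was calculated considering α = 0.05 and an 80% power (n = 16 per group"). A dropout allowance of a fifth brings this to 19, and the paragraph gives the resulting enrolment as "totaling 76 children and adolescents". It names no outcome, effect size or SD.
- Second, based on a previous study of occlusal splints and signs and symptoms of TMD: "Considering a mean difference between treatments equal to 2 (SD = 2), 3 groups". Power is again set at 80% and alpha at 0.05, and the result is that "a minimum of 30 subjects should be included in each group".

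Planned enrolment is the same throughout. The abstract says "The participants will be 76 children", and the Allocation procedure (1.3) has 76 numbered envelopes, with blocks of four.

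The number of groups is not the same throughout. The abstract and the Groups section (1.3.1) list three: controls without bruxism, infrared LED, and splint. The Photobiomodulation treatment protocol (1.5) gives Group 2 a red LED, Group 3 an infrared LED and Group 4 the splint.

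**The concern.** One paragraph holds two sizes per group, both at alpha 0.05 and 80% power, and does not say which governs. The larger is worded as a minimum, yet the planned total cannot supply it. The smaller, multiplied up, gives a total for a number of groups that the abstract and the list of groups do not have.

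At stake is whether the stated 80% power can be checked. It depends on how many groups share the 76 children and on which comparison is meant, and the article gives conflicting answers on the first. A reader who takes 30 per group as the requirement would call the trial too small. A reader who takes 16 would call it adequate. If the result is null, the two would interpret it differently.

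**Working it through.** **Inputs.** From Material and methods: difference 2, SD 2 (standardised difference d = 2/2 = 1), alpha 0.05, power 80%, 3 groups, 20% dropout, and the figures 16, 19, 30 and 76. Assumed, because the article does not state them: a two-sided test, equal allocation, and SD 2 as the between-child SD of the outcome compared.

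**1. The 16.** The normal approximation is n = 2 × (1.96 + 0.8416)² × (SD/difference)² = 2 × 7.849 × 1 = 15.7, so 16 per group. A t test needs 16.7, so 17. The first figure is therefore what difference 2 and SD 2 produce, although the article attaches those inputs to the second figure.

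**2. The 30.** The same inputs under the usual readings give:

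| Reading of the second calculation | n per group for 80% power | Power at 30 per group |
|---|---|---|
| One pair, unadjusted t test | 17 | 97% |
| Three-group ANOVA, third mean midway | 21 | 94% |
| One of three pairs, Bonferroni (alpha 0.05/3), t test | 23 | 92% |

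For the ANOVA row, means 0, 1, 2 have squared deviations that sum to 2, so the noncentrality is n × 2/2² = n/2. If instead two means are equal and the third differs by 2, the ANOVA needs only 16.

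None of these gives 30. Thirty appears only with unstated changes, for example a four-group ANOVA at 90% power with the two middle means midway. In an unadjusted t test, 30 per group has 80% power for about 0.74 SD, not 1 SD.

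**3. The total.** 4 × 19 = 76, while 3 × 19 = 57. Thirty per group needs 3 × 30 = 90 or 4 × 30 = 120. So 76 matches four groups of 19, and falls short of 30 per group with either number of groups.

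**4. What 76 delivers for d = 1 with 20% loss.**

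- Three groups: 76/3 ≈ 25 each, and 25 × 0.8 = 20 completers. Power is about 87% for an unadjusted pair, 79% for the three-group omnibus test and 74% for a Bonferroni-adjusted pair.
- Four groups of 19: 19 × 0.8 = 15.2, about 15 completers. Power is about 75% for an unadjusted pair (t test; 78% by the normal approximation).

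**5. Dropout.** 16 × 1.2 = 19.2, written as 19. Keeping 16 completers after 20% loss needs 16/0.8 = 20. The gap is one child per group.

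**The case against.** The strongest reply is that the 76 children may well be enough. A reader might infer from the clash that 76 and 80% power cannot both be true. The documents do not support that. In the three-group design of the abstract and the Groups section, 76 leaves about 20 completers per group, above the first calculation's 16, and unadjusted pairwise power is about 87% for a 1-SD difference. The article states no multiplicity adjustment in its calculation, so the 74% figure is not a failure of its own claim. This reply stands.

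Other strong readings also fail:

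- **That 76 is a multiplication slip and 57 was meant.** No section gives 57. The product is right for four groups, the treatment section describes a Group 4, and blocks of four are at least compatible with that. The fault is an unsettled number of arms.
- **That enrolment must rise to 90.** This would take the 30 as sound, but its own inputs do not yield it. Missing an unsupported minimum is an inconsistency in the text and does not by itself show a power deficit.
- **That the dropout allowance is a serious error.** The article says that 20% is added, and it does that to rounding. The shortfall is one child per group, and it vanishes if 76 children enter three groups.

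A further fair point is that the difference of 2 and SD of 2 come from a study of TMD signs and symptoms, whereas Analysis of results (1.8) names muscle activity and salivary markers as the dependent variables. Every power figure above therefore holds only for a 1-SD difference in whichever outcome is meant.

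What the reply leaves untouched is that both sizes are printed at the same alpha and power, that 30 cannot be derived as described, and that the total and the list of groups disagree. Condensing a protocol into an article does not explain contradictory figures in print.

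**Conclusion.** The paragraph is wrong as written and should be corrected before anyone relies on it. The sizes of 19 and 30 per group are not reconciled, and 76 meets the 30 in neither a three-group nor a four-group trial (90 or 120 needed). The 30 exceeds what its inputs require by 7 to 14 per group (23 down to 16) and would give 92% to 97% power instead of 80%. The 76 belongs to four groups, against the three in the abstract and the Groups section.

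The effect on power depends on the number of arms. Unadjusted pairwise power is about 87% with three groups and about 75% with four. This rests on a two-sided 5% test, equal allocation, a 1-SD difference and 20% loss. The article supports a finding of contradiction and of a figure that cannot be reproduced. It does not support a finding that the trial is underpowered.

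**What to change.** 1. Reconcile the number and content of the arms across the abstract, Material and methods, Groups (1.3.1) and the Photobiomodulation treatment protocol (1.5). Which set of arms is right is for the investigators to say.
2. Keep one sample size calculation. State its outcome, difference, SD, sidedness and the comparison it serves, and say why the difference and SD apply to that outcome.
3. Delete the 30 per group, or give the inputs that produce it.
4. State the total for the actual number of groups, and restate the power for it without changing enrolment. If the 1-SD assumption is kept, the figures are those in step 4 of the working: 87%, 79% or 74% for three groups, depending on the test, and about 75% unadjusted pairwise for four.
5. As a side point, divide by 0.8 for dropout instead of multiplying by 1.2.

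The cost is rewriting one paragraph and aligning the sections on groups. No extra children are needed. The downside is that the restated power may be less favourable than 80%.

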**Figure 1 F1:**
[figure not shown]
Standard protocol items: recommendations for interventional trials (SPIRIT) figure as recommended by 2013 SPIRIT statement.

**Figure 2 F2:**
[figure not shown]
Flowchart activity.

### Inclusion criteria

1.1

The sample will be composed of children in the mixed dentition phase (permanent incisors and molars erupted) and adolescents with an established permanent dentition.

### Exclusion criteria

1.2

Individuals with dental caries, those taking medications, such as anti-inflammatory agents, muscle relaxants, corticoids, anticonvulsants, and antidepressants, those with chronic diseases that affect muscles or motor coordination, and those who do not cooperate during the evaluation will be excluded from the study.

### Allocation procedure

1.3

Block randomization (groups of 4 participants) will be performed using sequentially numbered (1–76) opaque envelopes. The contents of the envelopes will be determined randomly with the aid of a computer program. Each envelope will contain a piece of paper stipulating the group to which the child/adolescent will be allocated. The envelopes will be sealed until the time of treatment.

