#### Groups:

1.3.1

The participants will be randomly allocated to the following groups:

Group 1: control—absence of bruxism.Group 2: bruxism treated with infrared LED.Group 3: bruxism treated with occlusal splint.

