### Photobiomodulation treatment protocol

1.5

The volunteers in Group 2 will be submitted to the initial evaluation of the morphological and psychosocial variables. During the same appointment, red LED (3 × 6 cm) will be administered using a board with 6 LEDs with a wavelength of 650 ± 20 nm, 7-minute operation time, optical spot of 5 ± 2 mm, and optical output of 2∼5 mW, with a dose of 2.675 J/cm^2^. Further analyses will be performed immediately after the photobiomodulation session and 1 week later. Group 3 will be submitted to the same analyses using an infrared LED protocol (wavelength: 850 ± 20 nm) with the same dose of 2.675 J/cm^2^.

The volunteers in Group 4 will be treated using the standard protocol of a rigid occlusal splint. After the initial evaluation, molds will be made for the fabrication of the splints, which will be delivered 1 week later. Written and verbal instructions for use will be given. After 1 month of daily use, the volunteers will return for the final morphological and psychosocial evaluations.

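### A single, published block length of 4 with visibly different treatments lets anyone who sees earlier allocations deduce some later ones, despite opaque envelopes

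*Protocol article*

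**What the plan says.** Section 1.3 (Allocation procedure) sets the method: "Block randomization (groups of 4 participants) will be performed using sequentially numbered (1–76) opaque envelopes". On how the sequence is made it says "The contents of the envelopes will be determined randomly with the aid of a computer program", and on timing "The envelopes will be sealed until the time of treatment". No other block length is mentioned.

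Section 1.3.1 (Groups) lists three groups: "Group 1: control—absence of bruxism.Group 2: bruxism treated with infrared LED.Group 3: bruxism treated with occlusal splint". Section 1.5 (Photobiomodulation treatment protocol) numbers them differently. There, Group 2 receives red LED, Group 3 infrared LED, and "The volunteers in Group 4 will be treated using the standard protocol of a rigid occlusal splint".

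LED is given at the appointment of the initial evaluation. For the splint, "molds will be made for the fabrication of the splints, which will be delivered 1 week later", followed by a month of daily use.

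Two entry decisions involve judgement. Section 1.2 (Exclusion criteria) provides that "those who do not cooperate during the evaluation will be excluded from the study". Section 1.4 (Evaluation of bruxism) rests the diagnosis on parent or caregiver report together with a list of clinical signs, with no threshold stated.

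**The concern.** Concealment has two parts. The next envelope must be unreadable, and it must also be unpredictable. Sealed opaque envelopes deal with the first. The second depends on what staff know about the sequence already used.

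Here the block length is constant and printed in the public article, and the treatment a child received is obvious to anyone who gives it or watches. Someone who has followed the earlier children in a block can therefore subtract what has been used and, near the end of the block, name what is left.

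This matters because entry is partly a matter of judgement. If the next allocation is known or suspected, the reading of a child's cooperation or of borderline clinical signs could shift, even unintentionally. The children entering LED and splint would then differ systematically. The planned mixed-model ANOVA (section 1.8) could not reliably repair that.

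**Working it through.** **The plan's own figure.** Section 3 (Material and methods) gives 16 per group plus 20%: 16 × 1.2 = 19.2, taken as 19. The total of 76 then requires four groups: 19 × 4 = 76, whereas 19 × 3 = 57. Also, 76 / 4 = 19 complete blocks. So the envelope count fits four groups, not the three listed in section 1.3.1.

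**Assumed observer.** The observer knows the block length and every earlier allocation in the block. This is an assumption; the article neither states it nor rules it out.

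**Scenario A: two bruxism arms, each block 2:2** (the article does not give the block composition).
- Certain: position 4 always; position 3 only if the first two are equal, probability 1/3. Sum 1 + 1/3 = 4/3 per block, and (4/3)/4 = 33.3%.
- Best guess correct by position: 1/2, 2/3, 2/3, 1. Sum 17/6 = 2.83, and 2.83/4 = 70.8%, against 50% by chance.
- For 2 × 19 = 38 children there are 9 complete blocks plus 2 children. The first two positions are never certain, so the expected number certain is 9 × 4/3 = 12. Over all 38, the best guess is right for 9 × 17/6 + 1/2 + 2/3 = 26.7, or 70.2%.

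**Scenario B: four groups, each once per block** (the layout that fits 76).
- Certain: position 4 only, so 25%, or 19 of 76.
- Best guess correct by position: 1/4, 1/3, 1/2, 1. Sum 25/12 = 2.08, and 2.08/4 = 52.1%, against 25% by chance.
- This treats membership of the bruxism-free group as an envelope outcome, which it cannot be, since diagnosis decides it.

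**Scenario C: three groups at equal ratio.** 4/3 is not a whole number, so a block of 4 cannot be balanced and predictability cannot be computed. The same obstacle arises if only the three treated groups of section 1.5 are randomised.

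**What varying the block length achieves.** This was simulated for two arms and 38 children. The guesser knows which lengths are possible but not where each block ends, and the lengths are equally likely.

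| Block lengths | Certain | Best guess right |
|---|---|---|
| 4 only | 32% | 70% |
| 4 and 6 | about 6% | about 69% |
| 4, 6 and 8 | about 2% | about 67% |

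Certainty nearly disappears; the guessing advantage barely moves.

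**Why not drop blocking.** With simple 1:1 randomisation of 38 children, the difference in arm sizes has standard deviation √38 ≈ 6.2. The chance of a difference of 4 or more is 1 − P(18, 19 or 20 in one arm) ≈ 63%.

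**The case against.** A computer-generated order in numbered, opaque, sealed envelopes is a genuine concealment method, and its order of events is largely right: cooperation is judged during the evaluation, and the envelope stays closed until treatment. The article does not say who screens, who holds or opens the envelopes, or who sees past allocations. An article may leave such roles to the full protocol, and their absence is not a fault. The diagnosis also rests partly on a questionnaire completed by parents or caregivers, which narrows staff discretion. All of this stands, and it makes the risk conditional.

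Three stronger readings are tempting, but the article does not support them.
- A reader might infer that everyone at the clinic learns each allocation and that the same people decide eligibility. The text does not say so.
- A reader might infer that upcoming allocations in general can be worked out. Even a fully informed observer is certain of only a quarter to a third; the rest are guesses, at best better than chance.
- A reader might apply the two-arm rate to all 76 envelopes and get about 25 foreseeable allocations (19 × 4/3). No version of the design has 76 children with bruxism in two arms.

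The visible difference is also clear only for LED against splint; red against infrared LED is less clear.

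What survives is that the article states one fixed block length and publishes it. That is a stated rule with a better alternative, not an omitted detail.

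**Conclusion.** The point holds in conditional form. A disclosed block length of 4, combined with treatments that reveal themselves, leaves some allocations deducible by anyone who has followed the block. Depending on the layout, 25% to 33% of allocations in complete blocks are certain (19 of 76 envelopes with four groups, or 12 of 38 children with two arms).

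The figures assume that recruiters know the block length and see earlier allocations, and that blocks are balanced as in scenarios A and B. They cannot be made firmer until sections 1.3, 1.3.1 and 1.5 agree on how many groups there are and which are randomised. Bias in the LED-splint comparison is possible, not demonstrated. The weakness is moderate and worth correcting because the correction costs so little.

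**What to change.** 1. Reconcile sections 1.3, 1.3.1 and 1.5 on the number and content of the groups. State that only children with bruxism are randomised between the treatment arms, and that the bruxism-free group is a non-randomised comparison group.
2. Replace the fixed block of 4 with randomly varying lengths that are multiples of the number of arms (for two arms, for example 4 and 6). Do not disclose the lengths to those who enrol. Keep blocking: unrestricted randomisation risks a large imbalance at this sample size.
3. Record and date eligibility, including cooperation, on the case form before each envelope is opened.
4. Because varying the length hardly reduces better-than-chance guessing, keep the running list of allocations from those who recruit.

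The cost is a different setting in the same computer program, a few sentences in the protocol and one dated entry per child. If recruitment stops inside a block of 6, two arms can differ by at most three children.
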